### Objectives

The specific aims of this study are to (1) evaluate whether medical gender affirmation improves HIV prevention and care outcomes over 12 months of follow-up, accounting for individual, interpersonal, and structural factors; (2) examine whether medical gender affirmation predicts 12-month prospective improvements in psychological functioning and health-related quality of life (HRQL) in TGD patients initiating hormone therapy adjusting for individual, interpersonal, and structural factors; and (3) characterize patient satisfaction with medical gender affirmation received, unmet needs and future desires, and barriers and facilitators of medical gender affirmation by age, race, ethnicity, gender identity, and HIV serostatus.

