### Statistical Considerations

The study outcomes are viral suppression (for TGD patients living with HIV); PrEP uptake (for TGD patients not living with HIV); and incident syphilis, gonorrhea, and chlamydia diagnoses by anatomical site (for all patients, irrespective of HIV status). The primary exposure is medical gender affirmation (hormones and surgery).

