### Data Analysis

Descriptive statistics (eg, frequencies, means, and standard deviations) will be obtained to summarize the variables. Bivariate tests (*t* tests or *χ*^2^) will examine differences by site. Subsequent analyses will use appropriate statistical procedures to adjust for site differences if necessary. Bivariate tests (*t* tests or *χ*^2^) will examine medical gender affirmation by HIV outcomes of interest, followed by multivariable regression models. Analyses will use SAS software with two-tailed tests and an alpha .05-level of significance.

Aim 1 analyses will involve descriptive statistics to characterize medical gender affirmation exposures and HIV prevention continuum (HIVPC) and HIV care continuum (HIVCC) outcomes at baseline and each follow-up over 12 months. We will model longitudinal HIV-related outcome trajectories as a function of medical gender affirmation using generalized estimating equations [74]. Models will be adjusted for individual, interpersonal, and structural covariates and confounders. Moderators (eg, age, race, and gender identity) will be tested to identify TGD patients at the highest and lowest risk of adverse outcomes. For example, we will evaluate whether racial or ethnic self-identification (people of color vs White) is an effect modifier of hormones and viral suppression (ie, whether there is heterogeneity in treatment effects by race). Analyses will be appropriately stratified for heterogeneous treatment effects.

In aim 2, we will longitudinally model within-person changes in mental health diagnoses and response to standardized behavioral assessments from baseline (prehormones) to 12-months (aim 2) among TGD patients prospectively initiating hormone therapy at cohort entry. Mediational models will test whether changes in mental health explain the effect of medical gender affirmation on improved HIVPC or HIVCC outcomes.

Aim 3 analyses will entail descriptive statistics to characterize patient satisfaction with medical gender affirmation received, unmet needs and future desires for medical gender affirmation, and barriers and facilitators of medical gender affirmation.

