**Lifetime hormone use** **(n=1756)**		
	Taken hormones	1456 (82.91)
	Have not taken hormones but interested in taking them	234 (13.33)
	Have not taken hormones and not interested in taking them	62 (3.53)
	Missing	4 (0.23)

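### Aim 2 is an uncontrolled pre-post comparison in hormone initiators, so its 12-month change cannot be attributed to hormones; the population for the mediation models is not stated

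*Protocol article*

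**What the plan says.** The Objectives section sets Aim 2 as whether "medical gender affirmation predicts 12-month prospective improvements in psychological functioning and health-related quality of life (HRQL) in TGD patients initiating hormone therapy", adjusted for individual, interpersonal and structural factors. The Data Analysis section gives the method: "we will longitudinally model within-person changes in mental health diagnoses and response to standardized behavioral assessments from baseline (prehormones) to 12-months", and the group is patients "among TGD patients prospectively initiating hormone therapy at cohort entry". The two sections agree on the population, and neither names patients who do not start hormones as a comparison.

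The same paragraph of Data Analysis closes with the mediation plan: "Mediational models will test whether changes in mental health explain the effect of medical gender affirmation on improved HIVPC or HIVCC outcomes". That sentence gives no analysis population and no exposure contrast. The Aim 1 paragraph above it says "We will model longitudinal HIV-related outcome trajectories as a function of medical gender affirmation using generalized estimating equations", without restriction to initiators. The Sample Size section contrasts hormones and surgery with none.

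Untreated patients are in the cohort. Table 5 lists 234 of 1756 survey patients under "Have not taken hormones but interested in taking them", and Table 4 lists 966 of 7821 warehouse patients with no current hormone prescription.

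**The concern.** The aim is worded as a question about what medical gender affirmation does, but its analysis has only a before and an after in people who all start treatment. Anything else that changes over the same 12 months enters the estimate. Patients may start hormones around the time they enter care, may enter when distress is unusually high, and may receive other services. Each would look like improvement after hormones.

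The article intends its findings to inform clinical care, so an uncontrolled change could be read as a treatment effect. The mediation models matter too. In the Conceptual Framework, psychological functioning and HRQL are the link between affirmation and HIV outcomes. If those models were run in the Aim 2 group, the hormone effect to be decomposed would carry the same confusion with time.

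**Working it through.** **No stated figure to reproduce.** The article gives no sample size or effect size for Aim 2 or for mediation. Its viral suppression figure of 182 (149 exposed, 33 unexposed; 51% versus 76%) does reproduce with the usual pooled two-proportion formula. It is a two-group calculation that belongs to Aim 1 and says nothing about Aim 2.

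**What can be separated from what.** Survey visits are at 0, 6 and 12 months (Study Recruitment and Cohort Enrollment Procedures). Let A = 1 for an initiator, and let E = A after baseline and 0 at baseline. The rank of the design matrix shows which terms can be estimated together.

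| Group | Terms | Rank / columns |
|---|---|---|
| Initiators only | intercept, E | 2 / 2 |
| Initiators only | intercept, A, E | 2 / 3 |
| Initiators only | intercept, E, linear time | 3 / 3 |
| Initiators only | intercept, E, visit 6, visit 12 | 3 / 4 |
| Initiators and concurrent non-initiators | intercept, A, E, visit 6, visit 12 | 5 / 5 |

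- Row 1: a pre-post change is estimable, but it is hormones plus everything else that goes with time.
- Row 2: no between-person hormone contrast exists, because A equals the intercept.
- Row 3: hormones can be separated from time only by assuming a straight-line time trend. The survey has a single pre-hormone visit, so that trend cannot be checked before treatment.
- Row 4: once time is left free, E is the sum of the two visit indicators and drops out.
- Row 5: a concurrent comparison group restores full rank.

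**Possible size of one component.** Regression to the mean gives an apparent improvement of d × (1 − r). Here d is the excess distress at entry in SDs above the usual level, and r is the baseline to 12-month correlation. The documents give neither, so both are assumptions:

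- d = 0.5, r = 0.5: 0.5 × 0.5 = 0.25 SD
- d = 0.5, r = 0.7: 0.5 × 0.3 = 0.15 SD
- d = 0: 0 SD for any r

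**Who could serve as comparison.**

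- Survey outcomes, including HRQL, which Table 1 collects by survey only: 234 never-users interested in hormones (234/1756 = 13.33%). Patients surveyed just before starting would probably give the same answer. The 234 should therefore be read as a pool that supplies both initiators and not-yet-treated time. The article does not give the split.
- EHR measures (mental health diagnoses and psychological distress in Table 1): 966 without a current prescription (966/7821 = 12.35%). This group may be mixed. In the survey, 57 ever-users were not currently on hormones and 62 never-users were not interested.

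**Mediation.** In its own wording the mediation sentence concerns the effect on HIV prevention and care outcomes, which is the Aim 1 effect. By position it follows the initiators-only sentence. The text does not settle which population is meant.

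**The case against.** Several points on the other side have force.

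- A reader might infer that exposure does not vary in Aim 2 and that nothing can be estimated. The documents do not support that. Hormone status changes within each person, and Statistical Considerations defines the exposure as hormones and surgery, so surgery can differ among initiators. The failure is in attributing the change to hormones.
- A reader might infer that the mediation models are confined to initiators and so cannot be identified. Only the sentence's placement suggests this. It can equally be read as decomposing the Aim 1 effect in the full cohort, where exposure varies. The supportable point is that the population is ambiguous.
- A reader might infer from the survey that mediation on viral suppression is impossible: applying 19 self-reported HIV-positive results in 1756 to the 234 gives 234 × 19 / 1756 = 2.5 patients. That ignores the warehouse, which holds 421 patients with HIV (Table 4) and EHR mental health data. Only HRQL as mediator is limited to survey patients.
- The Abstract places mental health and quality of life among secondary objectives. The primary outcomes and their power analysis are untouched.
- The article is condensed, Limitations admits self-selection into treatment, and sensitivity analyses for unmeasured confounding are planned.

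The last point does not remove the problem. The article itself fixes both the population and the contrast, so this is more than an omitted detail. Covariate adjustment cannot separate hormone start from visit when the two coincide, and a sensitivity analysis for unmeasured confounders does not supply a missing comparison group.

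**Conclusion.** The concern holds in a limited form. As written, Aim 2 can describe how initiators change over 12 months. It cannot say whether hormones, rather than time, entry into care or regression to the mean, produced the change. This follows from the design alone and needs no numerical assumption.

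How far the estimate would be off is unknown. The 0.15 to 0.25 SD range rests wholly on an assumed 0.5 SD excess at entry and a correlation of 0.5 to 0.7, and it falls to zero without that excess. For mediation, the finding is that the population must be stated. If the models were restricted to initiators, the hormone effect could not be separated from time. Viral suppression need not be excluded as an outcome.

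**What to change.** Amend the Aim 2 paragraph of Data Analysis:

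1. Add a comparison of initiators with concurrently followed patients who have not yet started. This uses observed starts only and does not alter anyone's care.
2. For survey outcomes, including HRQL, use never-users interested in hormones, counting their time as unexposed until they start (234 at the interim count).
3. For EHR measures, use warehouse patients without a current prescription (966), after excluding or separating past users and those not seeking hormones.
4. Treat initiation as time-varying and adjust for baseline score, site and calendar period.
5. Keep the initiators-only within-person change and label it descriptive.
6. State that the mediation models are run in the Aim 1 cohort, name the exposure contrast, and keep viral suppression among the outcomes.

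The cost is analysis wording and programming on patients already being followed, with no new data collection. The usable comparison groups will be smaller than 234 and 966 once initiators, past users and those not seeking hormones are separated out. Residual confounding between those who start and those who have not will remain, and should be covered by the sensitivity analyses already planned.

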### Study Recruitment and Cohort Enrollment Procedures

The IRB granted a waiver of written consent to allow automatic enrollment of all existing and new TGD adult patients at Fenway Health and Callen-Lorde, who meet the study’s eligibility criteria, into the LEGACY research data warehouse (RDW). Deidentified EHRs data (eg, provider-documented diagnoses, biomarker and laboratory data, and pharmacy records) and computerized self-administered patient-reported outcomes (PRO) captured as part of routine care (eg, screening for smoking, depression, and violence) are extracted from the EHR every 6 months. All patients identified as eligible and enrolled in the LEGACY RDW are approached, either in-person at clinic sites with provider permission or via secure email, and asked to complete an additional LEGACY survey at 3 time points over 12 months (baseline, 6 months, and 12 months) and complete optional HIV and STI testing as part of their routine patient care. For HIV and STI testing, a trained phlebotomist at a partner’s lab collected blood for HIV-1/2 antigen and antibodies (fourth generation; >99.7% sensitivity and 100% specificity) and for syphilis (rapid plasma reagin and treponema pallidium particle agglutination confirmatory) testing. Urine, vaginal, and anorectal swabs will be provider- or self-collected (depending on participant preference) to test for *Neisseria gonorrhoeae* and *Chlamydia trachomatis* via the APTIMA COMBO 2 Assay (Gen-Probe; >95.2% sensitivity and >96.8% specificity). Participants must be able to read and understand English or Spanish and be willing and able to provide informed consent to participate in the additional survey. Initial eligibility is assessed via the EHR; patients are asked to verify their eligibility before consenting to the survey.

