Missing data can create significant problems in the analysis or interpretation of longitudinal data. Statistical summaries will be used to describe the missing data. We will assess patterns of missing data between or within follow-ups [75-77], comparing patients in care with those who drop out of care. We will use modern missing data techniques as appropriate, such as multiple imputation [78,79]. The impact of unmeasured confounders will be evaluated via sensitivity analyses [80]. We will also test for heterogeneity of treatment effects in medical gender affirmation and HIVPC or HVCC outcomes, consistent with the PCORI (Patient-Centered Outcomes Research Institute) methodology standards.

Fenway Health is the lead for data analysis and the creation of analytic data sets. This group is staffed by doctoral and master’s level biostatisticians who have extensive experience analyzing health outcomes using various statistical approaches. For LEGACY, they will be the primary resource for statistical consulting on any future grant proposals, concept sheets, study design, statistical analyses, and manuscript preparation. A delineated concept proposal process is in place to facilitate collaborations or data requests for the cohort. Any requests for access to the analysis data sets require previous approval from the principal investigator and applicable oversight bodies such as PCORI or the Fenway IRB.

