### Cohort Recruitment, Enrollment, and Retention

The longitudinal cohort was approved by the IRB in January 2019. Prospective cohort enrollment began at Fenway Health in February 2019 and at Callen-Lorde in August 2019. Enrollment will continue through August 2020. As of April 2020, 7821 patients have been enrolled in the LEGACY RDW and 1756 have completed the additional baseline LEGACY survey. The baseline characteristics of the TGD patients in the RDW and survey are shown in Tables 4 and 5, respectively. Recruitment strategies that have demonstrated success include posting of study flyers in exam rooms and patient waiting areas (see Figure 3 for an example), educating providers about the study to facilitate successful patient referrals and linkages to the research (eg, presenting on the study to medical departments), and building a study identity that links to and is integrated with each clinical site’s transgender health program and services. Ongoing retention efforts consist of frequent reminder emails about upcoming survey participation and dissemination of study e-newsletters, which contain preliminary findings from the cohort to date (see Figure 4 for an example).

**Table 4 table4:** Baseline electronic health record data for transgender and nonbinary adult patients (N=7821).

Sociodemographics				Values^a^, n (%)

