**Result of most recent HIV test (n=1151)**		
	HIV positive	19 (1.65)
	HIV negative	1094 (95.05)
	Undetermined	7 (0.61)
	I do not know	25 (2.17)
	Missing	6 (0.52)

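### Survey respondents differ from the warehouse cohort, and neither the missing-data plan nor Aim 3 addresses survey non-participation, so pooled survey-only estimates are at risk of selection bias

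*Protocol article*

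**What the plan says.** Under Study Recruitment and Cohort Enrollment Procedures, the survey is meant for the whole warehouse: "All patients identified as eligible and enrolled in the LEGACY RDW are approached". Cohort Recruitment, Enrollment, and Retention gives the count so far: "As of April 2020, 7821 patients have been enrolled in the LEGACY RDW and 1756 have completed the additional baseline LEGACY survey". The same section adds "Enrollment will continue through August 2020" and "Prospective cohort enrollment began at Fenway Health in February 2019 and at Callen-Lorde in August 2019". Tables 4 and 5 describe the warehouse and the respondents separately.

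The missing-data text in Data Analysis promises summaries of missing data and an assessment of patterns across and inside follow-ups, "comparing patients in care with those who drop out of care". It allows modern methods where suitable and gives multiple imputation as an example. On the third aim it says "Aim 3 analyses will entail descriptive statistics to characterize patient satisfaction with medical gender affirmation received", together with unmet needs, desires, barriers and facilitators. Objectives asks for these by age, race, ethnicity, gender identity and HIV serostatus.

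Table 1 lists patient satisfaction, health-related quality of life, transgender integration, and stigma and discrimination as coming from the patient survey only. It lists viral suppression and PrEP uptake as coming from the health record and laboratory. The Abstract states that warehouse, survey and specimen data are linked.

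**The concern.** A patient who stays in care but never opens the baseline survey is neither a gap between follow-ups nor a drop-out from care. The plan as written has no step that looks at this group, although it was about three quarters of the warehouse at the interim count. Limitations mentions bias from sampling clinic patients and self-selection into treatment, but not self-selection into the survey.

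Pooled Aim 3 figures on satisfaction, unmet need and barriers are exposed most directly, because an unweighted description of respondents carries any selection straight into the result. Aim 1 models that adjust for stigma or transgender integration are exposed too, since those covariates exist only for respondents. Because the health record covers every non-respondent, part of the selection can be measured and corrected.

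**Working it through.** **Inputs.** Warehouse counts are from Table 4 and survey counts from Table 5. Comparisons with patients without a survey assume that the 1756 respondents lie within the 7821.

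**Tabled figures reproduced.** 4064/7821 = 51.96%; 1130/1756 = 64.35%; 421/7821 = 5.38%; 19/1151 = 1.65%. All agree with the tables.

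**Participation to date.** 1756/7821 = 22.5%.

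**Sex assigned at birth** (same item in both sources).
- Gap: 64.35 − 51.96 = 12.4 points; standardized difference 0.25.
- Among patients without a survey: (4064 − 1130)/(7821 − 1756) = 2934/6065 = 48.4% female; chi-square against respondents p < 0.001.
- Crude participation: 1130/4064 = 27.8% (female) and 610/3649 = 16.7% (male).

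**HIV status** (measures differ: health-record serostatus in all patients against the self-reported latest result among the 1151 ever tested).
- Expected positives among 1756 at the warehouse rate: 1756 × 0.0538 ≈ 95. Reported: 19.
- As a share of all respondents: 19/1756 = 1.08%. This counts everyone without a reported positive result as negative.
- Counting all undetermined, unknown and missing results among the tested as positive: (19 + 7 + 25 + 6)/1151 = 57/1151 = 4.95%, still below 5.38%.
- Also counting everyone unsure or missing on ever being tested: (57 + 106 + 90)/1756 = 253/1756 = 14.4%. This extreme is implausible, but it shows that the gap is likely rather than proven.

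**Race and ethnicity** (survey uses a single combined item, so part of the gap may be coding).
- Black: 4.33% against 13.68%.
- Hispanic or Latinx: 9.97% against 14.73%; among known values, 175/1741 = 10.1% against 1152/6245 = 18.4%.

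**Possible bias in a pooled estimate.** Bias from one imbalance = share gap × difference between the strata. The documents give no such differences, so 10 and 30 points are assumed for illustration.
- Sex, non-missing: 1130/1740 − 4064/7713 = 0.1225, giving a shift of 1.2 to 3.7 points.
- HIV: 19/1756 − 421/7821 = −0.043, giving 0.4 to 1.3 points.

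**Cost in precision of weighting.** Weight = warehouse share / survey share; effective n = (Σw)²/Σw².
- Sex only: weights 0.81 (female) and 1.35 (male); effective n ≈ 1632 of 1740; intervals wider by √(1740/1632) = 1.03.
- HIV only: weight 4.97 for positives with denominator 1756 (3.26 with 1151). With the former, effective n ≈ 1497 of 1756; intervals wider by √(1756/1497) = 1.08.

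**The HIV-positive stratum.** With n = 19, a proportion of 50% has a 95% Wilson interval of about 29% to 71%. Sample Size requires 182 patients living with HIV for viral suppression. The warehouse holds 421, but only 19 respondents reported HIV.

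**The case against.** The strongest objection is that this is a condensed article, and details of weighting are often left to a full protocol or analysis plan. That holds for the technical specification. It does not dispose of the point: the article does say which missingness will be examined, makes Aim 3 descriptive, and publishes the tables that show the imbalance.

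Other objections limit what can be claimed:

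- A reader might take 22.5% as the final response rate. The documents do not support that. Enrollment was open, one site began six months later, and the number approached is not given. Site timing may explain part of the difference in composition, and no site breakdown is shown.
- A reader might say that the plan handles drop-out only. It also covers gaps across and inside follow-ups and permits multiple imputation, which could draw on health-record data. It does not say that this would be used for non-participants.
- A reader might infer that the main HIV results are compromised. Viral suppression and PrEP uptake can be analysed in the whole warehouse, where 421 patients with HIV exceed the 182 required. Mental health diagnoses and psychological distress also have a health-record source.
- Under-representation of patients with HIV does not by itself bias an estimate within that group, and the survey's gender identity categories largely encode sex assigned at birth. The two main imbalances therefore act mostly on pooled figures. Selection on other characteristics could still act within strata.

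**Conclusion.** The point holds for survey-only measures, chiefly pooled Aim 3 estimates, and for Aim 1 models that adjust for survey-only covariates. The sex imbalance is firm, at 12.4 points on the same item. The HIV imbalance is probable: the survey percentage is 3.3 to 5.0 times lower depending on the denominator, with self-report set against the health record.

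A reader might infer that survey estimates will be biased. The documents show only a risk, because bias also requires the survey answers to differ by the characteristics that drive participation. On the illustrative 10 to 30 point differences, the sex imbalance alone moves a pooled percentage by about 1 to 4 points. Imbalances on several variables may add up or offset each other. The small number of HIV-positive respondents is a separate problem of precision, which weighting does not cure.

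**What to change.** Add the following to Data Analysis:

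1. Compare survey respondents with non-respondents on health-record variables, and name survey self-selection among the limitations.
2. Report pooled Aim 3 estimates weighted by the inverse probability of survey completion, beside the unweighted ones. Fit the participation model in all warehouse patients approached, or in all warehouse patients if approach is not recorded. Use site, age, race, ethnicity, sex assigned at birth, gender identity, hormone prescription, HIV status, PrEP, prior STI and visit count, all taken from the health record.
3. For Aim 1 models that adjust for survey-only covariates, use the same weights or imputation based on health-record data as a sensitivity analysis.
4. For Aim 2, fit any participation model among patients starting hormones. The all-warehouse weights do not carry over unchanged, since 87.65% of the warehouse already has a hormone prescription.
5. Give confidence intervals for Aim 3 results by HIV serostatus.

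The cost is one logistic model on data already linked, with no new data collection. Intervals widen: about 3% for sex alone and 8% for HIV status alone in the illustration above; a model with all the variables may cost more. The correction reaches only characteristics recorded in the health record.
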